### Missing values and data imputation

With regard to imaging data, only complete data sets will be accepted for analysis.

Missing values in the clinical dataset will initially be handled using the default preprocessing pipeline in the case that H2O AutoML is used. This pipeline applies median or mean imputation for numerical variables and mode imputation for categorical variables (https://docs.h2o.ai/h2o/latest-stable/h2o-docs/data-munging/imputing-data.html). In addition to this standard approach, we will evaluate alternative imputation strategies, particularly for approximately normally distributed numerical variables. These include, e.g., k-nearest neighbors (kNN) imputation, which leverages similarities across observations in the multivariate feature space and multiple imputation using chained equations (MICE), which incorporates multivariable relationships and reflects the uncertainty associated with imputed values.

Given the prospective nature of the study, we anticipate that most missing data will not be missing at random (NMAR), but rather occur systematically, for instance, due to early patient discharge or an inability to perform assessments as a result of clinical deterioration. In such cases, the absence of data may itself be informative with respect to the patient’s risk for postoperative complications. Therefore, in addition to the imputation techniques mentioned above, we will explore modelling strategies that explicitly account for informative missingness. These include the incorporation of missingness indicators (binary flags denoting whether a variable was observed or missing) and sensitivity analyses to assess the robustness of model predictions under different assumptions about the missing data mechanism.

The final approach to handling missing data will be selected based on a combination of model performance, diagnostic checks, and clinical plausibility.

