## Abstract

**Background:**

Postoperative pulmonary complications (POPC) are common after general anaesthesia and are a major cause of increased morbidity and mortality in surgical patients. However, prevention and treatment methods for POPC that are considered effective tie up human and technical resources. Therefore, the planned research project aims to create a prediction model that enables the reliable identification of high-risk patients immediately after surgery based on a tailored machine learning algorithm.

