### Eligibility criteria

Adult patients (≥18 years) of all sexes are eligible for the study.

Patients must meet the following **inclusion criteria**: Scheduling for elective surgical procedures under general anaesthesia with a planned overnight hospital stay, and written informed consent by patients.

If they meet any of the following **exclusion criteria**, they will not be included in the study: Younger than 18 years of age, outpatient surgery, planned postoperative admission to intensive care unit (ICU), need for intensive care treatment before surgery and emergency surgery.

**Secondary exclusion criteria** are: Unplanned hospital discharge/transfer on the day of surgery, which does not allow examination of the primary outcome; cancellation/postponement of index surgery; and immediate unplanned postoperative admission to the ICU due to an intraoperative complication.

Furthermore, the **Inclusion criteria for input data** are: At least two adjacent ribs and the pleura or corresponding pathologies (e.g., pneumothorax, pleural effusion) must be visible on the ultrasound image. The ultrasound examination must cover all 12 defined areas (details in chapter “Study measures”)**.**

The **exclusion criteria for input data** are: Ultrasound images on which the leading structures ribs and pleura or alternative pathologies cannot be depicted, or incomplete visualisation of the 12 previously defined examination areas in the thoracic region, e.g., in the case of immobile patients or inaccessibility due to a bandage or drains. Importantly, decisions regarding potential exclusion due to poor image quality will not be made by the examining physician, but rather by an independent, blinded radiologist, thereby minimising the risk of subjective selection bias.

Clinical data is collected from patients throughout their hospitalisation. An employee who is not involved in data collection will carry out a plausibility check and random comparison with the medical records at regular intervals. Implausible data is removed from the data record.

Patients who cannot be visited postoperatively and for whom no endpoint could be defined are excluded from the study; however, their data may be used for secondary analyses. Incomplete pre-operative routine data in the electronic patient record are not a reason for exclusion if the patient can be visited postoperatively

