### Study measures

Study-related measures to acquire the imaging data include performing a standardised lung ultrasound on each included patient immediately postoperatively in the recovery room or post-anaesthesia care unit (PACU). Sonographic examination of the lungs is a common, noninvasive bedside procedure. It can be performed without additional positioning in supine position and takes approximately 5 minutes. The examination is performed using a standardised, previously published method [13]. Thereby, a convex probe (5 MHz) and a predefined preset of the ultrasound device (the default “lung” preset of the device) are going to be used. Each hemithorax will be divided into 6 areas, separated by the anterior and posterior axillary lines (anterior, lateral, and posterior) and a superior and inferior area. For each patient, 12 pictures and 12 videos, one in each area, will be captured. This 12-zone protocol showed the highest intra-class correlation coefficient compared to other protocols [14]. A graphical representation of the areas can be found in Fig 2.

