**Fig 2 pone.0329076.g002:**
[figure not shown]
Graphic representation of the lung ultrasound areas. Lung ultrasound will be performed in 12 areas, 6 in each hemithorax. Areas are separated by the anterior and posterior axillary line into an anterior, lateral and posterior zone and a superior and inferior area.

The criteria for including imaging data are described above (“Eligibility Criteria”). If these conditions are not met, the interpretability of the ultrasound is considered insufficient.

To maximize inclusiveness and minimize selection bias, operators are encouraged to adjust technical parameters (e.g., depth and gain) during image acquisition in order to meet these quality criteria. A convex transducer was selected to allow visualization of deeper structures across a wide range of patient anatomies.

The performing physicians are experienced in perioperative medicine and critical care and will be trained in ultrasound methodology before the start of the study.

After transmission and storage in the PACS of the Department of Radiology, image pre-processing and artifact correction are performed before the data serves as input for the machine learning model. Images are not labeled by human experts; only the pre-defined endpoint POPC serves as labels for the imaging data.

The clinical data obtained for the study correspond to parameters routinely collected during anesthesiologic preoperative evaluation, the course of anaesthesia during surgery, and postoperatively in the recovery room. Plausibility checks are carried out on the numerical data; if these deviate from the valid value range, they are removed. Missing data may be imputed by different methods as described below.

Based on the collected data and the outcome parameters (description in chapter “Outcome”), machine learning algorithms will be trained to predict POPC by outputting an individual patient’s percentage risk of suffering a postoperative pulmonary complication.

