### Outcomes

The primary outcome of the PEPPERMINT study to be predicted by the machine learning model is the risk of developing postoperative pulmonary complications after surgery in general anaesthesia between postoperative days 1 and 7. POPC will be defined and graded by severity according to the standardised criteria of the StEP collaboration [1]. Complications not further described by the StEP collaboration will be defined as from the EPCO (European Perioperative Clinical Outcome) task force [20] as listed in Table 2. POPC, as a composite outcome, summarises atelectasis, pneumonia, acute respiratory distress syndrome (ARDS), pulmonary aspiration, pulmonary embolism, pleural effusion, pneumothorax, and bronchospasm [1]. POPC is assumed as soon as at least one of the listed events occurs and will be detected during the postoperative visit or chart review after the patient is discharged.

**Table 2 pone.0329076.t002:** Definition of postoperative pulmonary complications.

POPC	Definition/Diagnostic	Severity
Atelectasis	Detected on computed tomography OR chest radiography [1]	Mild: therapeutic supplemental oxygen <0.6 FiO_2_ Moderate: therapeutic supplemental oxygen ≥0.6 FiO_2_, requirement for high-flow nasal oxygen or both Severe: unplanned non-invasive mechanical ventilation, CPAP or invasive mechanical ventilation requiring tracheal intubation None: planned use of supplemental oxygen or mechanical respiratory support as part of routine care, but not in response to a complication or deteriorating physiology. Therapies which are purely preventive or prophylactic for example, high flow nasal oxygen or CPAP should be recorded as none

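### The stated reason for missingness indicators, early discharge, cannot apply to recovery-room predictors; flags built on it would carry post-prediction information into the clinical and combined models

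*Protocol article*

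**What the plan says.** **Prediction time.** The Abstract aims at "reliable identification of high-risk patients immediately after surgery". Under Study measures, the ultrasound is done in the recovery room or PACU.

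**Clinical inputs.** The text after Figure 2 in Study measures describes them as "parameters routinely collected during anesthesiologic preoperative evaluation, the course of anaesthesia during surgery, and postoperatively in the recovery room", and refers forward to the imputation section for missing values. Eligibility criteria is broader: "Clinical data is collected from patients throughout their hospitalisation".

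**Outcome.** The Outcomes section defines "the risk of developing postoperative pulmonary complications after surgery in general anaesthesia between postoperative days 1 and 7".

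**Missing data.** Missing values and data imputation expects most missing data to be not at random, for instance "due to early patient discharge or an inability to perform assessments as a result of clinical deterioration". It adds that the absence may itself say something about complication risk. It draws from this that strategies for informative missingness will be explored, among them the "incorporation of missingness indicators (binary flags denoting whether a variable was observed or missing") and sensitivity analyses. The final approach is to be chosen on model performance, diagnostic checks and clinical plausibility together.

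**The concern.** The mechanism and the remedy do not match. A missingness flag is a legitimate predictor when the gap is visible at the moment of prediction. Early discharge happens on the ward, after that moment. A flag driven by it records that the patient went home before a later visit, which is more likely after an uncomplicated course. Such a flag would help in the study data and would not exist in the recovery room, where the tool is meant to be used.

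At stake are the reported performance of the clinical and combined models, the comparison of either with ARISCAT, and the secondary question of whether clinical data improve on imaging. Choosing the missing-data approach partly on model performance would favour a flag of this kind.

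**Working it through.** The point is one of timing, and the plan gives no figure to reproduce. The sections are set side by side first. An illustration of size follows.

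**Timing**

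1. Inputs close in the recovery room (Study measures). The outcome window runs from day 1 to day 7 (Outcomes).
2. Unplanned discharge or transfer on the day of surgery that prevents outcome assessment is a secondary exclusion (Eligibility criteria). Early discharge in analysed patients therefore falls after the inputs are complete. The article uses discharge for leaving hospital.
3. What early discharge removes is the day 3 and/or day 7 visit. Modifications, adherence and concomitant care ends the study at discharge within 7 days. Data management keeps such patients if the day 1 visit is documented.
4. So early discharge produces missing visit data and cannot produce missing preoperative, intraoperative or recovery-room values.
5. Deterioration is not timed in the text. In the recovery room it could leave an input unrecorded, and that gap is known at prediction. On the ward it could not.
6. The hold-out patients described in Model training and evaluation come from the same study. If flags were built the same way there, the gain would pass into the test result and would not be exposed.

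**Illustration of size**

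Taken from the document: a reference AUROC of 0.83 (Sample size), used here as the true AUROC of a model without the flag. Assumed: a binormal score, a flag independent of the score given POPC status, and flag rates p0 (without POPC) and p1 (with POPC). The POPC rate does not enter the AUROC.

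- d = √2 × z(0.83) = √2 × 0.9542 = 1.349, so d² = 1.821 and d√2 = 1.908.
- A flagged patient's log likelihood ratio shifts by s₁ = ln(p1/p0), an unflagged patient's by s₀ = ln[(1−p1)/(1−p0)].
- AUROC with flag = Σ P(case's flag) × P(non-case's flag) × Φ[(d² + s_case − s_non-case)/(d√2)], summed over the four flag combinations.

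Worked case, p0 = 60% and p1 = 20%: s₁ = ln(0.2/0.6) = −1.099 and s₀ = ln(0.8/0.4) = 0.693.

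| Flagged | Weight | Φ | Product |
|---|---|---|---|
| both | 0.2×0.6 = 0.12 | 0.830 | 0.0996 |
| case only | 0.2×0.4 = 0.08 | 0.506 | 0.0405 |
| non-case only | 0.8×0.6 = 0.48 | 0.971 | 0.4660 |
| neither | 0.8×0.4 = 0.32 | 0.830 | 0.2656 |
| sum | 1.00 | | 0.872 |

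The same formula over a range of assumed rates, with flag-only AUROC = 0.5 + (p0 − p1)/2:

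| p0 / p1 | Flag alone | With flag | Gain over 0.83 |
|---|---|---|---|
| 50% / 50% | 0.50 | 0.830 | 0.000 |
| 50% / 40% | 0.55 | 0.833 | 0.003 |
| 50% / 30% | 0.60 | 0.841 | 0.011 |
| 50% / 20% | 0.65 | 0.855 | 0.025 |
| 60% / 20% | 0.70 | 0.872 | 0.042 |
| 70% / 15% | 0.775 | 0.903 | 0.073 |

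A weak association adds almost nothing and a strong one adds several hundredths. The document does not show which applies.

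**The case against.** A reader might infer that the protocol commits itself to leaking the outcome into its models. The text does not support that. Flags are one option to be explored, beside sensitivity analyses, and clinical plausibility is among the selection criteria. Study measures already ends the clinical inputs in the recovery room and points forward to the imputation section, so the authors may have meant flags for those inputs only. The statement that data are collected throughout the stay can simply cover outcome data. No sentence makes a ward-visit variable a predictor, and the full variable list may stand in the SAP (S3 File), which is not at hand. All of this stands. It does not rescue the rationale: if flags are confined to recovery-room inputs, early discharge is no reason for them.

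A reader might also infer that much of the planned gain from 0.83 to 0.93 could be spurious. That too goes beyond the documents. The primary objective concerns the imaging model, which accepts only complete image sets and has no evident use for flags. An inflated clinical model would make the imaging-versus-clinical comparison harder for imaging to win. The rates in the illustration are assumptions.

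Two further limits apply. That discharge or deterioration is a consequence of POPC is an inference: deterioration can have other causes, and within the recovery room it may be a valid signal. Nor is outcome follow-up after discharge ignored, since chart and discharge-letter review is planned and a documented day 1 visit is required.

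**Conclusion.** The concern holds as a mismatch between the stated cause of missingness and the proposed remedy. Early discharge cannot explain gaps in the declared inputs, so the rationale needs correcting on either reading. Leakage is conditional: it arises only if flags are built on visit data, as the rationale suggests and the section does not rule out. It would then affect the clinical and combined models, favour them over ARISCAT, and go unnoticed in cross-validation and in the hold-out set.

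The size cannot be determined from the document. Under the assumptions above it runs from about 0.00 to 0.07 AUROC above 0.83. The point should be corrected before final modelling. It does not undermine the primary imaging objective.

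**What to change.** Add to Missing values and data imputation: *Predictors and missingness indicators are restricted to variables due to be recorded before the patient leaves the recovery room. Indicators for recovery-room assessments that were due but not done are allowed. No variable or indicator from the ward visits, discharge or later enters any model.*

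In the same section, separate missing predictors from missing outcome data. Describe visits missed through early discharge as incomplete outcome follow-up, and examine them in a sensitivity analysis, in addition to the chart and discharge-letter review already planned. Carry the same wording into the SAP if it is not already there.

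The cost is a few sentences, a timestamp filter in the data pipeline and one sensitivity analysis. No data collection changes. Trial status reports 150 of the planned 512 patients included, so the change can precede final modelling. The only loss is a gain in apparent performance that could not be had at the bedside.

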### Secondary models and endpoints

In addition to the prediction models, we aim to extract specific predictive markers which might be evaluated in an additional study. Once established and evaluated with additional studies, both the AI models and the marker might help to identify high-risk patients, allowing for the adaptation of treatment at an early point of care.

In addition to the primary binary classification model for the presence or absence of POPC, the study will explore the development of additional models that aim to distinguish between different types and severities of complications. These extended models will incorporate more granular outcome definitions, including the timing of complication onset and the presence of multiple complications in a single patient.

Moreover, secondary predictive models will be constructed to estimate outcomes such as quality of postoperative recovery, length of hospital stay, and in-hospital mortality. Important features will be identified based on variable importance metrics. Comparisons between patients with and without complications will be conducted using appropriate statistical tests, including t-tests or Mann-Whitney U tests for continuous variables, and chi-squared or Fisher’s exact tests for categorical variables.

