**Methods:**

This clinical cohort study will follow the TRIPOD statement for multivariable prediction model development. Development of the prognostic model will require 512 patients undergoing elective surgery under general anaesthesia. Besides the collection of perioperative routine data, standardised lung sonography will be performed postoperatively in the recovery room on each patient. During the postoperative course, patients will be examined in a structured manner on postoperative days 1,3 and 7 to detect POPC. The endpoints determined in this way, together with the clinical and imaging data collected, are then used to train a machine learning model based on neural networks and ensemble methods to predict POPC in the early postoperative phase.

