### Objectives

The main hypothesis of the PEPPERMINT study is that a patient’s risk of POPC can be reliably predicted using a machine-learning algorithm and that the predictive accuracy of the algorithm outperforms common clinical scoring systems.

The primary objective is to develop a machine-learning algorithm based on immediately postoperatively obtained lung ultrasound imaging data of adult patients undergoing surgery in general anaesthesia to predict the risk of postoperative pulmonary complications. This model is intended to provide better predictive ability than the currently best-established clinical score, the ARISCAT [5] or a machine learning model solely based on clinical routine data.

The secondary objective is to investigate whether improving model performance by adding clinical routine parameters to the imaging data is possible.

Furthermore, the optimal risk threshold for an intervention will be determined in case of a clinical application of the model.

Further objectives include identifying patient-specific risk factors for POPC through analysis of the collected routine clinical data and modification of the models created to predict the secondary endpoints of hospital length of stay, in-hospital mortality and postoperative quality of recovery.

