**Mental status**	
	Overall score of the Mini-Cog test (3-word-recall-task and clock drawing test)

Table 3 contains parameters that are collected on postoperative visits on day 1,3 and 7; CPAP = continuous positive airway pressure, CRP = C-reactive protein, diast. = diastolic, FiO_2 _= fraction of inspired oxygen, ICU = intensive care unit, NIV = non-invasive ventilation, paCO_2 _= partial pressure of arterial carbon dioxide, paO_2 _= partial pressure of arterial oxygen, PACU = post-anaesthesia care unit, PCT = Procalcitonin, syst. = systolic.

Additionally, after hospital discharge, relevant pulmonary imaging, diagnoses or complications are extracted from the discharge letter.

Postoperative recovery and patient satisfaction as a secondary outcome parameter are going to be evaluated with the Quality of Recovery-9 (QoR-9) questionnaire (Table 4) on day 1,3, and 7 [22]. The score ranges from 0 to 18, with a higher score indicating a better subjective recovery.

**Table 4 pone.0329076.t004:** Quality of recovery-9 questionnaire.

QoR-9-Questions	Score
Had a feeling of general well-being.	Not at all = 0 points Some of the time = 1 point Most of the time = 2 points
Had support from others (especially doctors and nurses).	
Been able to understand instructions and advise. Not being confused.	
Been able to look after personal toilet and hygiene unaided.	
Been able to pass urine and having no trouble with bowel function.	
Been able to breathe easily.	
Experiencing headache, backache or muscle pains	Not at all = 2 points Some of the time = 1 point Most of the time = 0 points
Experiencing nausea, dry-retching or vomiting	
Experiencing severe pain or constant moderate pain	

The table was adapted from [22]; The article was published under the Creative Commons Attribution (CC BY 4.0) license (https://creativecommons.org/licenses/by/4.0/). QoR-9 = Quality of recovery-9.

Other secondary outcome parameters, hospital length of stay and in-hospital mortality, will be determined by a chart review after hospital discharge.

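### The protocol commits without condition to an in-hospital mortality model, but at assumed death rates of 0.5% to 5% the 512 patients give about 3 to 26 deaths, too few to develop or validate it reliably (minor)

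*Protocol article*

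**What the plan says.** Under Objectives, after the primary and secondary objectives and the risk threshold, the Protocol article lists further aims. One is "modification of the models created to predict the secondary endpoints of hospital length of stay, in-hospital mortality and postoperative quality of recovery". The section Secondary models and endpoints repeats this as a firm plan: "secondary predictive models will be constructed to estimate outcomes such as quality of postoperative recovery, length of hospital stay, and in-hospital mortality". The next sentence says that important features will be identified from variable importance. No condition on the number of deaths is attached in either place. The paragraph just before, on models for type and severity of complication, promises only exploration.

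The cohort is described in the abstract: "Development of the prognostic model will require 512 patients undergoing elective surgery under general anaesthesia". Eligibility criteria excludes, among others, "planned postoperative admission to intensive care unit (ICU), need for intensive care treatment before surgery and emergency surgery". A secondary exclusion removes "immediate unplanned postoperative admission to the ICU due to an intraoperative complication". The Outcomes section says that "hospital length of stay and in-hospital mortality, will be determined by a chart review after hospital discharge".

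Sample size derives 512 only from the POPC comparison (AUROC 0.93 against 0.83, significance level 0.05, power 80%). It also says that the three ARISCAT risk groups are recruited in about equal numbers.

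**The concern.** What a prediction model can learn, and how precisely its discrimination can be measured, depends mainly on the number of patients in the rarer outcome class. For POPC that number is comfortable: the preliminary cohort had 111 cases in 259 (43%). The section on overfitting and class imbalance expects only moderate imbalance on that basis. This expectation cannot be carried over to death, which has no stated rate and is being studied in an elective cohort from which emergencies and three kinds of intensive-care patient have been removed.

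If the plan is followed as written, the study will report a mortality model, an AUROC and a list of important predictors resting on very few deaths. Readers could take that list as a finding of a prospective study when it mostly reflects the particular patients who died.

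**Working it through.** **Inputs from the Protocol article.** N = 512; POPC 111/259 = 43% in the preliminary cohort; AUROC 0.83 and 0.93, significance level 0.05, power 80%; hold-out of newly enrolled patients, size not stated.

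**Assumptions.** In-hospital mortality of 0.5% to 5%; true AUROC of the mortality model 0.80; where a hold-out is shown, 102 patients (20% of 512), for illustration only.

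**1. The plan's own figure.** The document gives no expected number of deaths to reproduce. Its 512 concerns POPC and does not follow from the stated inputs alone, because prevalence, sidedness and the correlation between the curves are not given with it. With the Hanley-McNeil variance, a two-sided test and no correlation, a prevalence of 43% gives 266 and an assumed prevalence of 19.5% gives 510. So 512 is not shown to be wrong, and nothing below depends on it beyond N itself.

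**2. Expected deaths and precision.** Expected deaths = 512 × rate. The Hanley-McNeil variance for d deaths and s survivors is

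Var = [A(1 − A) + (d − 1)(Q1 − A²) + (s − 1)(Q2 − A²)] / (d·s), with Q1 = A/(2 − A) and Q2 = 2A²/(1 + A).

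For A = 0.80: Q1 − A² = 0.6667 − 0.64 = 0.0267 and Q2 − A² = 0.7111 − 0.64 = 0.0711.

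Example with d = 10, s = 502: (0.16 + 9 × 0.0267 + 501 × 0.0711) / 5020 = 36.03 / 5020 = 0.00718. The SE is 0.085 and the half-width is 1.96 × 0.085 = 0.17.

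| Assumed mortality | Expected deaths in 512 (95% binomial range) | 95% half-width of AUROC, all 512 used | Expected deaths in 102 | Chance of no death in 102 = (1 − rate)^102 |
|---|---|---|---|---|
| 0.5% | 2.6 (0–6) | 0.30 (d = 3) | 0.5 | 60% |
| 1% | 5.1 (1–10) | 0.23 (d = 5) | 1.0 | 36% |
| 2% | 10.2 (5–17) | 0.17 (d = 10) | 2.0 | 13% |
| 3% | 15.4 (8–23) | 0.14 (d = 15) | 3.1 | 4.5% |
| 5% | 25.6 (16–36) | 0.10 (d = 26) | 5.1 | 0.5% |

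For comparison, 43% of 512 is about 220 POPC cases. The same formula with 220 cases and 292 non-cases gives 26.69 / 64,240 = 0.000416, SE 0.020 and half-width 0.04.

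**3. Illustrative hold-out of 102.** With 2 deaths and 100 survivors: 7.23 / 200 = 0.0361, SE 0.190, half-width 0.37. With 5 deaths and 97 survivors: 7.09 / 485 = 0.0146, SE 0.121, half-width 0.24. With no death, AUROC and sensitivity are undefined. At 1% mortality, 10 deaths would need about 10 / 0.01 = 1,000 new patients.

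**4. Development.** On the common rule of thumb of ten events per predictor, k predictors need a mortality of 10k/512: 2.0% for one, 9.8% for five, 19.5% for ten. In five-fold cross-validation at 1% there is about 5.1/5 = 1 death per fold.

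**5. Cross-check through POPC.** If all deaths arose among the 220 expected POPC cases, an assumed case fatality of 1%, 2%, 5% or 10% would give about 2, 4, 11 or 22 deaths. This is the same range.

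**The case against.** The strongest reply has several parts.

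- **The rate is assumed.** This is correct: no document gives one. A reader might infer that the cohort can yield only a handful of deaths. The documents do not support that. It holds up to about 2%; at 3% to 5% there would be 15 to 26.
- **Recruitment is enriched.** Equal ARISCAT groups make about a third of patients high-risk and a third intermediate, and the preliminary cohort had a median age of 66 and 43% POPC. Both push mortality above that of an unselected elective population. This stands, and it is why the range runs to 5%.
- **The exclusions are narrower than they may look.** Only immediate ICU admission caused by an intraoperative complication is removed. Patients who deteriorate later stay in, and chart review covers the stay beyond day 7. This also stands.
- **A model can be fitted.** A reader might infer that fitting or evaluation is impossible. That goes too far. The protocol allows built-in R functions, regularisation and restricted complexity, and a very small penalised model could be fitted. But these measures do not supply events, so instability and imprecision remain.
- **The hold-out size is not given.** The 102 is an illustration, not a consequence of the plan. The conclusion does not need it, since the figures on all 512 already show the problem up to about 3%.
- **The statistical analysis plan may set a minimum event count.** It may, and its absence from the article is not the point. The point is that the article states the model as certain.
- **The aim is exploratory.** This stands, and it limits the weight of the point.

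**Conclusion.** The concern holds in a limited form. The protocol commits, as a further objective, to an in-hospital mortality model and a ranking of its features, on a sample sized for POPC and with several high-risk groups excluded. Across assumed rates of 0.5% to 5%, about 3 to 26 deaths are expected. Even the top of that range gives a half-width of about 0.10 with every patient used for evaluation, and it falls well short of what a multi-predictor, AutoML or deep-learning model needs. Such a model could not be developed reliably or validated usefully, and its variable importance would be largely noise.

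The conclusion rests on the assumed mortality range and on an assumed AUROC of 0.80. It does not show that no mortality model can be fitted. The primary POPC analysis and the other secondary models are unaffected. Severity: minor.

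**What to change.** In Objectives and in Secondary models and endpoints, state that in-hospital deaths will be reported descriptively: count and rate with an exact 95% confidence interval, overall and by POPC status and ARISCAT group. Add that a mortality model, with any feature ranking, will be built only if a prespecified minimum number of deaths is reached, and will otherwise be dropped. The minimum can be justified by the precision wanted, using the formula above. If the statistical analysis plan already contains such a rule, align the article with it. Keep the length-of-stay and quality-of-recovery models.

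The cost is a few sentences and the possible loss of one exploratory model. Trial status reports 150 patients included and recruitment still open, so the change can be made before the analysis.
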